## Abstract

**Objective:**

The efficacy of alcohol reduction applications is variable, and the underlying factors are largely unknown. The aim of this study is threefold: evaluate the relationship between user engagement and intervention efficacy, investigate the efficacy of the different functions applied, and investigate the efficacy of the intervention application compared to control groups.

**Methods:**

A randomized controlled trial will be conducted to determine the efficacy of a newly developed smartphone application compared to the controls in reducing alcohol consumption at a 30, 60, 90, 120, 150, and 180 days follow‐up. Hazardous drinkers, aged 18 years or older, will be recruited through web articles and will be randomized (blinded to their allocation), to receive one of the two versions of the application (educational or control application) for 30 days, or will be allocated to a wait‐list control group. Function usage times will be recorded on a single‐user level to determine the association between application usage and efficacy.

**Results:**

Data collection will be completed by July 2020, and follow‐up will be completed by January 2021.

**Conclusions:**

The evaluation of intervention efficacy as a function of user behavior will hopefully contribute to the science of developing more efficient alcohol intervention applications in the future.

AbbreviationsANCOVAanalysis of covarianceAUDITAlcohol Use Disorders Identification TestBCTbehavior change techniqueDBCIdigital behavior change interventioneBACestimated blood alcohol concentrationUK unitUnited Kingdom unit (8 grams or 10 ml of pure alcohol)

## INTRODUCTION

1

Excessive alcohol consumption is a significant public health problem (Brick, 2004) and a leading cause of death worldwide according to the latest statistics of the World Health Organisation (2014). Brief interventions delivered in health care settings to hazardous drinkers are effective (Kaner, 2010), but have limited reach due to lack of time, training, or financial resources (Heather, Dallolio, Hutchings, Kaner, & White, 2004; Kaner, 2010). In the past decade, there have been major advances in digital behavior change interventions (DBCIs) to help individuals with alcohol use disorders (Zhang, Ward, Ying, Pan, & Ho, 2016).

As Crane (2017) summed up, nine out of 10 meta‐analyses or systematic reviews of DBCIs concluded (Carey et al., 2009, 2013; Dedert et al., 2015; Donoghue, Patton, Phillips, Deluca, & Drummond, 2014; Kaner et al., 2017; Khadjesari, Murray, Hewitt, Hartley, & Godfrey, 2011; Riper et al., 2011, 2014; White et al., 2010) that DBCIs reduce the amount of alcohol consumed, the frequency with which it was consumed and/or problems related to its consumption, relative to control conditions (Crane, 2017). Effect sizes in DBCIs were mostly small (ranging from *d* = 0.20 to *d* = 0.42) and indicated a mean reduction in consumption of approximately 24 g of alcohol, or 3 UK units of alcohol per week (range 12–33 g; Crane, 2017). It is important to note that the aforementioned DBCIs have been provided on the web. Although smartphone applications have the potential to help people manage their behavior in various health‐related fields, like physical activity, smoking or healthy diet (Bort‐Roig, Gilson, Puig‐Ribera, Contreras, & Trost, 2014; Bricker et al., 2014; Coughlin et al., 2016, respectively), there is limited evidence for the effectiveness of applications aiming to foster safe alcohol consumption (Garnett, Crane, Michie, Wesr, & Brown, 2016). According to Attwood et al.'s (2017) results, engaged users showed a significant reduction in alcohol consumption after the first week of application usage (mean −4.9 UK units), with no further improvement over time (week four mean reduction was −3 UK units). Gonzalez and Dulin (2015) found a reduction in hazardous drinking days among alcohol‐dependent users over a 6‐week trial compared to a bibliotherapy group. Gajecki et al. (2017) found a skill training smartphone app to be successful in reducing the likelihood of excessive alcohol consumption among excessively drinking university students both at 6 and 12 weeks post‐intervention. Also, they reported a reduction in the quantity of drinking at 6 weeks post‐intervention and a reduction in the frequency of drinking both at 6 and 12 weeks post‐intervention. To conclude, studies investigating smartphone applications that aim to reduce the consumption of alcohol reported positive outcomes, with varying effectiveness.

A major issue in application development is engaging users with the application content and features, reflected by the high drop‐off rates; 95% of applications are not used longer than a month (Milward et al., 2016). To date, relatively few studies were conducted to explore user preferences in relation to alcohol consumption reduction applications (Attwood, Parke, Larsen, & Morton, 2017). Earlier studies relied on the user ratings of publicly available applications (Crane, Garnett, Brown, West, & Michie, 2015), or on the evaluation of targeted sample groups (Gajecki, Berman, Sinadinovic, Rosendahl, & Andersson, 2014; Milward et al., 2016). The findings of these studies indicate that user preferences include personalized content, social networking capability, and ease of functionality, especially in terms of entering drinking data (Attwood et al., 2017). Zhang et al. (2016) reported that notifications and information sharing were the most useful components, while psychotherapeutic aspects (including a functional analysis chart and a behavioral goals chart) were the least useful feature of their mobile application, based on user self‐reports. Crane, Garnett, Michie, West, and Brown (2018), in a factorial design study, found that the combination of normative‐feedback and cognitive bias retraining and self‐monitoring and feedback and action planning yielded improvements in alcohol‐related outcomes after 4 weeks. Attwood et al. (2017) analyzed the data of the large user base of a publicly available application (Drinkaware), completed with user interviews, and a common preference was expressed for more personalized content (Attwood et al., 2017).

Although the above studies have a great contribution to our understanding of user preferences in mobile applications reducing alcohol consumption, the link between application usage and efficacy is not fully understood yet. According to Milward, Deluca, Drummond, and Kimergård (2018), user engagement—that is, how long and how often the participant uses the intervention (Crutzen et al., 2011)—is a significant predictor of intervention efficacy. In case of low user engagement, an application is unable to promote behavioral changing progress (Fitzgerald & McClelland, 2017), thus exploring the correlation between user engagement and intervention efficacy to reduce harmful alcohol consumption is a key research objective.

To investigate this question, a new smartphone alcohol intervention application was developed—Yoozan—with built‐in timers recording usage times of the different functions separately for every user. A randomized controlled trial will be conducted, where participants will use Yoozan or a control application (with restricted functionality, described in Methods) for 30 days, or will be allocated to a wait‐list control group. By analyzing usage times and the efficacy of the application in reducing the amount of alcohol consumed, the primary aim of the study is to evaluate the relationship between user engagement and intervention efficacy. The secondary aim of the study is to investigate the efficacy of the application functions by investigating the relationship between usage times of the application functions and intervention efficacy. The tertiary aim of the study is to investigate the efficacy of the intervention application compared to an active control application and to a wait‐list control group.

We hypothesize that there will be a positive correlation between engagement (reflected in usage time) and between the extent of reduction in alcohol consumption. We also hypothesize that Yoozan users will consume less alcohol at post‐intervention and 30, 60, 90, 120, 150, and 180 days follow‐up, compared to the participants in the control conditions.

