### Recruitment of study participants and trial flow

2.2

Recruitment took place from December 2019 and is currently ongoing. Participants are recruited through promotion articles published on Hungarian Internet portals. In the articles, Yoozan is introduced with a call to participate in testing in case the reader wants to change his/her drinking habits. All interested participants are directed to the webpage of the study, from where the application can be downloaded. Based on a block randomization method, an equal number of participants download either Yoozan, the control application, or allocated to the wait‐list control group. After installing the application, participants are asked to read the participant information sheet and provide informed consent and a valid email address for which usability questionnaire and follow‐ups will be sent (see Figure 1).

Participants allocated to the wait‐list group are informed that 6 months later, the application will be sent to their email addresses and are encouraged to fill a few tests (7‐day Timeline Followback, Alcohol Use Disorders Identification Test [AUDIT]) with instant feedback.

Study inclusion criteria are informed consent via the Web form to ensure knowledge of procedures and the declaration of consent; participant age ≥18 years, to ensure a minimal age of participation; ownership of an Android‐operating smartphone and at least weekly Internet access, to ensure program access; a screening AUDIT score ≥8 out of 40, to include adults with potentially hazardous or harmful alcohol consumption; and an indication of an attempt to reduce alcohol consumption (screening motivation score ≥2 out of 5), to ensure a minimal willingness to change. Exclusion criterion is participation in other treatments for the reduction of alcohol consumption, to avoid confounding treatment effects.

The study targets Hungarian speaking users; thus, the language of the intervention is Hungarian. If the intervention is effective, translation to English and upload to App Store and Google Play is planned.

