### Measures

2.4

At baseline weekly alcohol consumption, AUDIT score, motivation to change drinking habits, and sociodemographic data (age and gender) are assessed. Weekly alcohol consumption is assessed by the 7‐day Timeline Followback (e.g., see Sobell & Sobell, 1992) by users entering the consumption for each day of the previous week from a predefined list of drinks. It allows defining consumption measures that hopefully contribute better comparability between studies (Shorter et al., 2019), such as the frequency of drinking and heavy drinking (on a weekly level) and the summed consumption in standardized units. The AUDIT is a validated 10‐item screening tool developed by the World Health Organization (WHO) to assess alcohol consumption, drinking behaviors, and alcohol‐related problems. It is particularly designed for health care practitioners, but with suitable instructions, it can be self‐administered (Babor, Higgins‐Biddle, Saunders, & Monteiro, 2001). Motivation to change drinking habits is measured with the question “How important is it for you to change your drinking habits?” with five options to answer (1: not important, 5: very important).

The follow‐up questionnaires consist of the 7‐day Timeline Followback and application usability test. Subjective rating of application functions is measured at the first (30 days) follow‐up, with questions regarding the perceived effectiveness of each function helping to reach alcohol‐related goals, with five options to answer (1: very poor, 5: very helpful).

Besides the self‐administered tests, usage times of the application are recorded, and the following variables are formed: total usage, frequency (the number of usage sessions), and usage time of functions.

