The selection of tracked states was determined by states/moods known to be influenced by excessive alcohol consumption. A decrement in attention‐related cognitive abilities and memory functions are well documented in case of a hangover (e.g., Anderson & Dawson, 1999; McKinney & Coyle, 2004), thus a tracked state is (1) *intellectual sharpness*. Fatigue and a poor sense of well‐being are symptoms of a hangover (Wiese, Shlipak, & Browner, 2000), which is manifested in the state of (2) *energy level* and (3) *overall rating of the day*. Also, acute stress may produce an increase in alcohol consumption (de Wit, Söderpalm, Nikolayev, & Young, 2006), thus tracking (4) *stress level* in relation to alcohol consumption might help users to recognize a potential trigger of drinking. Also, Andersson, Söderpalm, and Berglund (2007) reported a positive relationship between reported stress reduction and the amount of alcohol consumed.

The application consists of three functional units: (1) registration and feedback, (2) core functions, and (3) educational modules (see Table 1 and Figure 2 for an overview).

**TABLE 1 mpr1848-tbl-0001:** An overview of the functions

Functional unit	Function	Rationale
Registration (present in Yoozan, control application and wait‐list groups)	Baseline tests (weekly alcohol consumption, AUDIT, and motivation to change)	Set pre‐intervention baseline
	Personalized feedback (weekly alcohol consumption and AUDIT)	Presenting drinking profile and normative comparison, as effective tools for reducing harmful alcohol consumption (Miller et al., 2013)
Core functions (present in Yoozan and control application groups)	Drink, activity, and mood diary	Providing a platform for clear, organized tracking of alcohol related data
	eBAC calculator	Calculating and displaying the estimated blood alcohol level
	Achievements	Creating goal commitment and providing additional feedback
	Role models	Promoting non‐problem drinking, harm reduction or abstinence
	Activity planner	Encouraging alternative activities other than alcohol consumption
	Community chat	Providing peer support
Modules (present only in Yoozan)	Module 1—consequences of excessive alcohol consumption and goal setting	Facilitating conscious evaluation of the effects of alcohol on ones' life
	Module 2—facilitate action planning and problem‐solving	Presenting a problem‐solving technique with practical information on how to prevent excessive alcohol intake

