### Control application

3.5

The control application has the same core functions as Yoozan, without the educational modules. With the exception of WHO alcohol consumption guidelines, core functions do not contain explicit information on alcohol use. Thus, the rationale behind applying a control application was to investigate the effectiveness of the core functions in reducing alcohol consumption, without providing information on alcohol‐related topics.

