## RESULTS

4

The composition of our sample will be demonstrated via descriptive statistics of participants' age, gender, and baseline 7‐day Timeline Followback, AUDIT measures, and motivation to change scores. Random imbalances between the intervention and control groups will be examined using chi‐squared tests. To evaluate the efficacy of the intervention, a repeated measure one‐way between‐groups analysis of covariance (ANCOVA) will be conducted. The analysis model will be built with group allocation as the independent variable, change in alcohol consumption as the dependent variables (the difference between baseline and follow‐ups 7‐day Timeline Followback in consumed alcohol units, binge drinking occasions, and drinking frequency), and age, sex, and motivation to change as covariates. Prior to the analysis, we will make sure that the specific assumptions for normality and homogeneity of variance for the one‐way ANCOVA will be met. In situations where data is missing—for example, with participants who are lost to the 6‐month follow‐up—the mixed model approach will be used to estimate missing values.

Multilevel modeling will be used to estimate the relationship between change in alcohol consumption (consumed alcohol units, binge drinking, and drinking frequency), application usage (total usage time, usage frequency, and usage time of functions) and application usability ratings in the educational and control application groups.

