## DISCUSSION

5

This study protocol describes the design of a randomized controlled trial with the following aims: (1) evaluate the relationship between user engagement and intervention efficacy, (2) investigate the efficacy of the application functions by investigating the relationship between usage time of the application functions and intervention efficacy, and (3) investigate the efficacy of the educational application compared to an active control application and to a wait‐list control group. To the best of our knowledge, this will be the first study to take behavioral data into account in the evaluation of the effectiveness of a complex alcohol reduction application on a large sample. Crane et al. (2018) recorded usage times in a factorial design study, with no significant differences between application components. They also found that application components in combinations led to improvements in alcohol‐related outcomes (Crane et al., 2018), supporting the conclusion of Webb et al. (2010), that effectiveness increases with the number of BCTs. Zhang et al. (2016) found in their self‐report study that notifications and information sharing were the most, while psychotherapy was the least useful feature of their mobile application. Attwood et al. (2017) observed mixed feedback regarding the usefulness of the individual features, which emphasizes the heterogeneity of user needs.

With an attempt of taking the continuously growing knowledge of the field into account, we developed a mobile application, Yoozan, with a wide range of functionality: self‐monitoring and feedback; action planning; normative feedback; identity change; community support; goal setting; evaluation of progress; and mood‐diary. We assume that functions/components in a complex application will compete for usage, resulting in different usage times in an ecologically valid context. By registering usage time of functions on the single‐user level, it is possible to examine application efficacy as a function of usage habits such as usage time, usage frequency, the number of used functions, and usage time of functions. This data will serve as useful guidance for future application development, helping to specify effective functions and user behaviors associated with high efficacy.

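### Efficacy of the educational modules is to be read from self-selected usage time, although access to them as a package is randomised; module claims should rest on the allocation, and usage slopes should be reported as associations

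*Protocol article*

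**What the plan says.** The secondary aim in the Introduction is to "investigate the efficacy of the application functions by investigating the relationship between usage times of the application functions and intervention efficacy". Under Measures, "the following variables are formed: total usage, frequency (the number of usage sessions), and usage time of functions". The Results section, which holds the planned analysis, states: "Multilevel modeling will be used to estimate the relationship between change in alcohol consumption", "application usage (total usage time, usage frequency, and usage time of functions") and usability ratings in the two application groups. It names age, sex and motivation as covariates for the ANCOVA of the group comparison, and names none for the multilevel model. The Discussion intends the usage data to help identify which functions are effective. It also says "We assume that functions/components in a complex application will compete for usage", so time per function is the user's choice. The limitations listed there do not include self-selected usage.

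Access to the modules, by contrast, is allocated. Table 1 heads that block "Modules (present only in Yoozan"). Section 3.5 says "The control application has the same core functions as Yoozan, without the educational modules". Under block randomisation "an equal number of participants download either Yoozan, the control application" or join the wait-list. The tertiary aim compares Yoozan with the control application and with the wait-list.

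**The concern.** How long a person spends in a module is decided after randomisation, by that person. Someone more determined to cut down may both read more and drink less. Usage also accumulates over the same 30 days as the first outcome change, so early success may itself prolong use, and baseline covariates cannot remove that. A positive slope of reduction on module time is therefore no evidence that the modules work.

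For the modules this weakness is avoidable at package level. Module use is zero by design in the control application and optional in Yoozan, which is randomised access with one-sided non-compliance. If the multilevel model compares users within Yoozan, the module coefficient rests only on who chose to read. If it pools the two application groups, it mixes that choice with the randomised contrast.

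At stake is what the trial may conclude. A statement that the modules are effective could be drawn from an observational slope while the randomised comparison shows nothing.

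**Working it through.** **Inputs from the protocol.** Sample size section: d = 0.20, 80% power, two-sided 5%, 394 per group, 27% response at the first follow-up, 4356 recruited. No power is given for the usage aims.

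**The plan's own figure.** The two-sample t-test for d = 0.20 needs 394 per group (power 0.8006), as stated. Responders per arm from the total: 4356/3 = 1452, and 1452 × 0.27 = 392. Inflating 394 gives 394/0.27, rounded up to 1460 per arm or 4380 in total, 0.6% above 4356. The difference does not affect this point; 392 or 394 responders per arm are used below.

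**Assumptions, not in the documents.** Inert modules; one unmeasured trait with the same correlation r with module use and with reduction; complete outcomes among responders. Two simulation set-ups:

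- A: 392 per arm, 60% of Yoozan users open a module, slope of log(1 + time), 4000 trials per setting.
- B: 394 per arm, all Yoozan users have some log-normal module time, 2000 trials per setting.

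Share of trials with a falsely significant result (nominal 5%):

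| r | A: slope within Yoozan | B: slope within Yoozan | B: both apps pooled | Allocation-based test, A / B |
|---|---|---|---|---|
| 0.1 | – | 5.5% | 5.6% | – / 4.5% |
| 0.2 | 9.9% | 10.5% | 8.2% | 4.4% / 4.9% |
| 0.3 | 39.1% | 31.6% | 21.9% | 5.1% / 4.6% |
| 0.4 | 84.9% | 76.1% | 56.9% | 5.8% / 5.2% |

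**Effect of adjustment on the within-Yoozan slope.**

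- A, adding an item that correlates 0.5 with the trait: 7.4%, 25.4% and 64.4% at r = 0.2, 0.3 and 0.4.
- B, adding a motivation score of reliability 0.5: 11.8% at r = 0.3; of reliability 0.8: 6.3%.
- A, adding six core-function usage times with the same loading: about 19% at r = 0.3 and about 32% at r = 0.4; with the 0.5 item as well, about 15% and 26%.

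**Complier-average effect of the package.** Estimate = (Yoozan mean − control-app mean) / share of Yoozan users opening at least one module. Its test is that of the randomised difference, so power is unchanged: 80% at 394 per arm and d = 0.20. If that difference is 0.20 SD, the effect in users is 0.20/0.75 = 0.27, 0.20/0.50 = 0.40 or 0.20/0.25 = 0.80 SD.

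The 95% half-width, with unit SD and uptake treated as known, is 1.96 × √(2/392) / uptake = 0.14 / uptake:

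- 80% uptake: 0.18 SD
- 60% uptake: 0.23 SD
- 40% uptake: 0.35 SD

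**Selective response.** Take 1452 per arm, inert modules, a trait correlating 0.3 with reduction, and 27% response at the average trait value. Let response depend on the trait in Yoozan only, with log-odds 0.3, 0.5 or 0.8 per SD. The allocation contrast among responders is then biased by 0.06, 0.11 or 0.15 SD and falsely significant in 14%, 32% or 59% of trials.

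**The case against.** The strongest reply is that the randomised safeguard is already planned. The tertiary comparison of Yoozan with the control application is the unconfounded test of the module package. Dividing it by uptake gives the same test on another scale. This stands: a reader might infer that the trial has no randomised test of the modules, and the protocol does not support that.

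Second, one binary allocation cannot answer which function matters. It is tempting to read the complier-average effect as showing which module is inert. It cannot separate Module 1 from Module 5, and it says nothing about core functions, which both applications contain. The control-app versus wait-list contrast can test those only as a package. This also stands.

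Third, the 5% error rate of the allocation-based test assumes that response is unrelated to the trait. With 73% expected loss, and randomisation before eligibility assessment, that is doubtful. The randomised estimate is therefore not free of bias, though selective response threatens the usage model as well.

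Fourth, the high false-positive rates depend on assumed confounding. At r = 0.1 there is almost no inflation, and adjustment lowers the rest. The 85% is no forecast for this trial.

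Fifth, much of the text speaks of correlation and relationship. But the aim itself speaks of efficacy, and the Discussion intends to identify effective functions. What remains is that these causal statements rest on usage time.

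**Conclusion.** The point holds in a limited form. Usage-time slopes cannot carry statements on function efficacy. With inert modules the within-Yoozan slope is falsely significant in about 5% to 85% of trials over r = 0.1 to 0.4, and less often after adjustment; every value in that range rests on an assumed correlation.

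For the five modules as a package, the protocol already contains a better basis in the randomised Yoozan versus control-app contrast. A complier-average effect adds the size of the effect in those who use the modules; it is not an additional test. It relies on allocation acting only through opening a module, and on response not being selective. The first is reasonable if the applications are otherwise identical, but section 3.3 lists goal-setting as a core function while Table 1 places it in Module 1, so the two must be reconciled. That Module 3 feeds the activity planner does not by itself break the assumption, since this path runs through module use.

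**What to change.** In the planned analysis:

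1. State that conclusions on module efficacy rest on the randomised Yoozan versus control-app contrast.
2. Add the complier-average effect of opening at least one module. Define uptake in advance, use two-stage least squares with allocation as instrument, and include the same baseline covariates as the group comparison. State that it applies to the module package.
3. Accompany both with a sensitivity analysis for outcomes missing selectively by arm.
4. Adjust the function-level usage models for baseline consumption, AUDIT and motivation, and report them as associations. Reword the secondary aim and the Discussion to match, and add self-selected usage to the limitations.
5. Reconcile where goal-setting belongs and say which users can reach it.

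The cost is a paragraph, one extra model on usage data already logged, and a sensitivity analysis; no new data are needed. The downsides to state are a wide interval if uptake is low, the exclusion assumption, and possible bias from selective response.
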